#### Safety assessment and adverse events

During the study period, the researchers will record the adverse events at any time and assess whether they are related to the intervention. If they are related to the intervention, the intervention will be stopped immediately and recorded in the CRF form and report to the Ethics Committee of Zhejiang Hospital, and the participants will be given appropriate financial compensation. Adverse events occurring in the different treatment regimens in this study will statistically compared to evaluate the safety of the different treatment regimens. The safety evaluation is graded as follows:

Grade 1: safe, without any adverse reactions; no abnormality in the safety index examination.Grade 2: relatively safe, with mild adverse reactions, can continue the treatment without any treatment; no abnormality in the safety index examination.Grade 3: safety concerns, moderate adverse reactions, and treatment can be continued; safety indices are mildly abnormal.Grade 4: Discontinue the study due to serious adverse reactions or if there is an obvious abnormality in the safety index examination.

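### The safety section orders an immediate stop for any related adverse event, yet its grading lets treatment continue after mild and moderate adverse reactions

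*Protocol article*

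**What the plan says.** Everything at issue stands in one section of the protocol article, Safety assessment and adverse events.

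- **Relatedness.** Every event is to be judged for its link to treatment: "the researchers will record the adverse events at any time and assess whether they are related to the intervention".
- **Stopping statement.** "If they are related to the intervention, the intervention will be stopped immediately and recorded in the CRF form". The same sentence adds a report to the ethics committee and financial compensation. It does not mention severity.
- **Use of the data.** "Adverse events occurring in the different treatment regimens in this study will statistically compared to evaluate the safety of the different treatment regimens".
- **Grade 2.** "Grade 2: relatively safe, with mild adverse reactions, can continue the treatment without any treatment".
- **Grade 3.** "Grade 3: safety concerns, moderate adverse reactions, and treatment can be continued", with mildly abnormal safety indices.
- **Grade 4.** "Discontinue the study due to serious adverse reactions or if there is an obvious abnormality in the safety index examination".

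Grade 1 covers participants with no adverse reaction and raises no question here.

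**The concern.** The stopping statement depends on relatedness alone. The grading depends on severity and on the safety examination. A related mild or moderate reaction falls under both, and they give opposite answers: one requires a stop, the other permits continuation.

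Three things are at stake.

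- **Patient safety.** The test intervention includes a sudden thrust to the neck, given over 12 sessions. The Discussion itself acknowledges that the safety of cervical rotational manipulation remains a worry. Whether sessions go on after a related event should not depend on which sentence the practitioner has in mind.
- **Treatment received.** The reading that is applied decides who completes the course, and so how much treatment lies behind the comparison of heart rate variability between groups.
- **The safety result.** Adverse events are to be compared between regimens. Grades 2 to 4 are worded partly by whether treatment can go on or must end, so the decision to stop may influence the grade that is written down.

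**Working it through.** No arithmetic applies: the point does not depend on any error rate, effect size or sample size, and the plan gives no figure to reproduce. The check sets the two statements side by side for each kind of related event.

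| Related event | Stopping statement | Grading | Agree? |
|---|---|---|---|
| Mild | Stop at once | Grade 2: may continue | No |
| Moderate | Stop at once | Grade 3: may continue | No |
| Serious | Stop at once | Grade 4: discontinue | Both end treatment |

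**Step 1: is the stopping statement limited anywhere?** Its only condition is relatedness. The rest of the article, including the three intervention descriptions and the follow-up section, neither restricts it to serious events nor ranks it against the grading.

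**Step 2: can the permissive wording of the grades remove the conflict?** Grades 2 and 3 say that treatment can go on, not that it must. But a mandatory stop leaves nothing to permit. If the stopping statement is always obeyed, the continuation wording in Grades 2 and 3 never applies to a related reaction.

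**Step 3: could Grades 2 and 3 refer only to unrelated events?** The article does not say so. The grades follow directly on the aim of evaluating the safety of the regimens, and reactions unrelated to treatment would not serve that aim. The usual meaning of an adverse reaction also points to a link with treatment.

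**Step 4: do the statements agree fully for serious events?** They agree that treatment ends. They differ on what is ended: the stopping statement names the intervention, while Grade 4 names the study. The article does not say whether a participant stopped under either statement remains in the study.

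**The case against.** The best defence is that the grades are an evaluation scale and not instructions. They are introduced as a way of grading the safety evaluation, straight after the sentence on comparing events between regimens. On that view, the phrase on continuing only describes how bad the reaction was, and a participant who was stopped could still be graded 2 or 3. Part of this stands: it would be too strong to say that the grade is defined by continuation, since severity and the safety indices also enter. But it only softens the conflict. Grade 4 plainly names an action, and a reader at the bedside will take Grades 2 and 3 as permission.

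It is also true that both statements end treatment for serious related events, so the conflict is confined to the milder ones. That the article condenses a fuller protocol does not help: the objection is to two explicit statements that disagree, not to missing detail.

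A reader might be tempted to infer more, and the document does not support it:

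- **That the sample-size allowance is exceeded.** The allowance takes 27 to 30 per arm, which is 30 − 27 = 3 participants. Setting a number of stopped participants against it needs a reaction rate, which the article does not give. It also treats stopping the intervention as loss from the study, which the stopping statement does not say.
- **That nobody would be stopped under the grading.** Grades 2 and 3 permit continuation without requiring it, so the number stopped could be zero or more.
- **That the arms will be handled differently.** The Blinding section says that the manipulative therapists know the allocation, so this is possible. Nothing in the safety wording differs by arm, and there is no evidence that it would happen.
- **That rules for assessing and analysing participants who stop are missing.** An article may leave these to the full protocol or the analysis plan.

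**Conclusion.** The contradiction is real and is wrong as written. It is confined to related mild and moderate events. The conclusion rests on the wording alone and on one assumption: that adverse reactions in Grades 2 and 3 include reactions related to treatment, which is the natural reading and which nothing in the article excludes.

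Its size cannot be stated. Without adverse event rates, neither the number of participants affected nor any effect on the heart rate variability comparison can be calculated. The case for correcting it rests on participant safety and on the fact that staff cannot comply with both statements, not on a demonstrated bias or loss of power.

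**What to change.** In Safety assessment and adverse events, the investigators should:

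1. Reconcile the stopping statement with Grades 2 to 4, so that each combination of relatedness and severity leads to one stated outcome. The clinical content is for them to decide, including whether it should be the same for manual treatment and for tablets.
2. State whether the stop in the first statement and the discontinuation in Grade 4 each mean ending the intervention or ending participation in the study.

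The cost is a one-paragraph protocol amendment with notification of the ethics committee. No extra visits, procedures or participants are needed.

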**Methods/design:**

In this study, 90 participants will be randomly assigned at a 1:1:1 ratio into a test group (cervical fixed-point rotational manipulation manipulation group), a control group (sham manipulation group), or a Western medicine control group, with 30 participants in each group. All participants will be treated for a period of 4 weeks. The primary outcome indicators assessed is the HRV-related parameters, and the secondary outcome indicators are the NDI scale, NPQ scale, and HAMA scale. The assessment time points will be before and after treatment. The follow-up visits will be the first and sixth months after the end of treatment.

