### Intervention

#### Test group (cervical fixed-point rotation manipulation group)

Muscle relaxation: the participant will assume the prone position or sitting position; the practitioner will relaxe the muscles with traditional Tui Na techniques; and the doctor will relaxe the muscles of the neck, shoulder, and upper back with kneading, plucking, and pinching. This method focuses on pressing and kneading at the strips or hard knots with points, plucking, and generally finds pressure points or hard knots in the trapezius, sternocleidomastoid and transverse cervical vertebrae, and kneading and kneading techniques are performed for approximately 10–15 min. Once the muscles are relaxed, the following points will be massaged and stimulated with the thumb or elbow joint: Fengfu (DU16), Fengchi (Gb20), Yamen (DU15), Jiaji points of cervical (EX-B2), Dazhui (DU14), Jingbailao (EX-HN14), Tianzong (SI11), Neiguan (PC6), Waiguan (SJ5), Hegu (LI4), Ashi point. Table 1 shows the location of the acupuncture points.Cervical localized rotation manipulations: Rotation manipulations will be applied precisely to the diseased cervical vertebral segment according to the specifics of the examination and imaging; for example, the C2 spinous process deviates to the right side, or the small joints are misaligned. After muscle relaxation, the patient will assume a sitting position, and the physician will stand behind the patient’s right side, with the right thumb against the patient’s C2 spinous process and the remaining four fingers placed on the contralateral side of the lower neck to help. The participant’s head will be bowed with the lower jaw placed in the practitioner’s right elbow socket, the face will be tilted to the right, and the practitioner will hold the participant’s left mandibular angle with the lower arm of the right hand to assist, the practitioner’s right arm will be the participant’s head upward support, the participants will be exert upward pulling and stretching force, and then the participant’s head will be placed to the right side lateral flexion to the maximum limit and then slightly turned to the left side, and then the head right lateral flexion movement will be suddenly increased to an amplitude of approximately 3–5°. The left thumb simultaneously will push the cervical spinous process to the left, at which point a popping sound can be heard. At the end of the manipulation, whether the cervical spinous process distortion is corrected; if the distortion is still present, the above maneuver will be repeated 2–3 times. The course of treatment will be as follows: once every other day, three times a week, four consecutive weeks of treatment, for a total of 12 times. Follow-ups will be conducted 1 month and 6 months after the end of treatment.

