#### Western medicine group

Mecobalamin (Eisai China Pharmaceutical Co., Ltd., 500 μg/tablet) 500 μg/dose, 3 times a day, supplemented with celecoxib capsules (Pfizer Pharmaceutical Co. Ltd., 0.2 g/capsule) 0.2 g/d, 1 time/d, for pain relief in those with obvious pain, for a duration of 4 weeks. Follow-ups will be conducted one month and six months after the end of treatment.

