#### Follow-up observation

Patients will be monitored posttreatment, with follow-up assessments conducted at one month and six months. These assessments will be conducted either in person at the hospital or via telephone, and home visits will be arranged as necessary. The primary method of data collection involve the administration of questionnaires. For those demonstrating substantial improvement in panic and palpitations and significant changes in heart rate variability, an ambulatory electrocardiogram will be conducted at the time of follow-up to assess the long-term effects of manipulative therapy.

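### Adverse events are to be compared across all three regimens, but the text gives the manual arms 12 treatment contacts and the drug arm none, so contrasts with the drug arm will tend to under-count its mild, transient events

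*Protocol article*

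**What the plan says.** **The planned comparison** (Protocol article, Safety assessment and adverse events): "Adverse events occurring in the different treatment regimens in this study will statistically compared to evaluate the safety of the different treatment regimens".

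**How events are collected** (same section): over the study period, "the researchers will record the adverse events at any time and assess whether they are related to the intervention". The section names no common visit, call, diary or recall period.

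**Contact in the manual arms** (Test group): "once every other day, three times a week, four consecutive weeks of treatment, for a total of 12 times". The sham-group section gives the same course.

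**Contact in the drug arm** (Western medicine group): tablets, plus capsules "for pain relief in those with obvious pain, for a duration of 4 weeks". After that course only the follow-ups at one and six months are mentioned.

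**Time points shared by all arms.** The abstract says "The assessment time points will be before and after treatment". Follow-up observation adds "Patients will be monitored posttreatment, with follow-up assessments conducted at one month and six months".

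**Test and size.** The Statistical analysis section assigns count data to the chi-square test at the 5% level. Each arm has 30 participants.

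**The concern.** If events are written down as they come to light, the chance that an event is recorded depends on how often the participant is in front of someone who can record it. On the stated schedules that frequency is fixed by the arm. Soreness or dizziness after a session can be mentioned at the next session within days. A brief stomach upset on tablets may have passed before the drug arm's next stated contact.

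A difference in recorded events between a manual arm and the drug arm would then mix a true difference in harm with a difference in opportunity to report. The likely direction is under-counting in the drug arm. That makes manipulation look less safe than it is relative to the drugs, and it can hide a true excess of drug-arm events. Analysis cannot recover events that were never elicited.

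Safety is a declared interest of the trial: the Background hopes to confirm it and the Discussion calls it a continuing concern. The drug arm is the only comparator without manual treatment.

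**Working it through.** The plan gives no figure for adverse events, so there is none of its own to reproduce. Only the arm size of 30 enters below; it agrees with the plan's own step from 27 evaluable participants, 27 / 0.9 = 30.

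**Step 1. Contacts during treatment, as stated.**
- Test: 3 per week × 4 weeks = 12.
- Sham: the same, 12.
- Western medicine: none stated, so 0.
- Adding the end-of-treatment assessment that all arms have: 13, 13 and 1.
- After treatment: 1 month and 6 months in every arm, hence equal.

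**Step 2. Bias formula.** Let the true risk of an event be *p* in both arms, with capture probability *c*M in a manual arm and *c*D in the drug arm. The recorded proportions are *p* × *c*M and *p* × *c*D, and their ratio is *c*M / *c*D. The true risk cancels, so the false ratio depends on capture alone.

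**Step 3. Illustration.** Every risk and capture value here is an assumption; the documents supply none. The last column is the exact probability that an uncorrected chi-square test of 30 versus 30 gives p < 0.05 although the true risks are equal.

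| True risk | Capture, manual / drug | Expected participants with a recorded event | False ratio | Rejection |
|---|---|---|---|---|
| 10% | 90% / 90% | 2.7 v 2.7 | 1.00 | 5.2% |
| 10% | 90% / 70% | 2.7 v 2.1 | 1.29 | 5.8% |
| 10% | 90% / 50% | 2.7 v 1.5 | 1.80 | 8.2% |
| 20% | 90% / 90% | 5.4 v 5.4 | 1.00 | 5.0% |
| 20% | 90% / 70% | 5.4 v 4.2 | 1.29 | 7.2% |
| 20% | 90% / 50% | 5.4 v 3.0 | 1.80 | 14.8% |
| 40% | 90% / 90% | 10.8 v 10.8 | 1.00 | 4.8% |
| 40% | 90% / 70% | 10.8 v 8.4 | 1.29 | 9.8% |
| 40% | 90% / 50% | 10.8 v 6.0 | 1.80 | 27.9% |

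For example, at 20% risk: 0.20 × 0.90 = 0.18 and 0.20 × 0.50 = 0.10, so 0.18 / 0.10 = 1.8.

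**Step 4. Masking.** Suppose the drug arm truly has the higher risk, 20% against 11.1%. With capture of 50% and 90%, the recorded proportions are 0.20 × 0.50 = 0.10 and 0.111 × 0.90 = 0.10. A true ratio of 1.8 would appear as no difference.

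**Step 5. Equal capture.** Setting *c*M = *c*D returns the ratio to 1.0 and the rejection rate to about 5% at any of these risks. That is already the position for test versus sham, with 12 sessions each.

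**The case against.** The strongest objection is that the schedule is not visible. Figure 2 is not shown and a journal article condenses a fuller protocol, so calls or dispensing visits in the drug arm may exist there. This stands, and it makes the point conditional. It does not remove the point, because the visible text itself sets out unequal contact and an unrestricted comparison across regimens. Even a weekly drug-arm contact would leave 12 against 4.

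Several stronger readings are tempting, and the documents do not support them:
- A reader might infer that drug-arm participants are at home and report from four weeks' memory. The text says neither. Recruitment includes wards, so some may be seen often, and the recording rule could cover events that participants volunteer.
- A reader might treat the abstract's before-and-after time points as the schedule for collecting events. That sentence follows the list of outcomes and concerns their assessment.
- A reader might count 12 contacts against 1. That credits the end-of-treatment visit to one arm only; the consistent counts are 12 against 0, or 13 against 1.
- A reader might quote a 1.8-fold false excess as the expected bias. It rests wholly on assumed capture rates. At 70% capture the rejection rate is only about 6% to 10%.

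It can also be said that an independent recorder and a standard printed form are planned (Data collection and management), and that the safety grading draws partly on examination findings that do not depend on memory. Both narrow the problem, but neither equalises the opportunities to report. Moderate or serious reactions would probably be known in every arm by week 4, so the distortion falls mainly on mild events. Its likely direction also works against the therapy under test, though that does not help where it masks a drug-arm excess.

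**Conclusion.** The point holds in a limited, conditional form. On the visible text, recording events as they arise and comparing all regimens makes capture depend on an arm-specific contact frequency: 12, 12 and 0 stated contacts during treatment. Unless the unseen schedule equalises the asking, both contrasts with the Western medicine arm will tend to under-count that arm's mild, transient events. Test versus sham is not affected by this.

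The documents do not allow the bias to be sized. The range of 1.3 to 1.8 for the false risk ratio assumes equal true risk, 90% capture in the manual arms and 70% to 50% in the drug arm. Nor do they support saying that the comparison is already shown to be confounded. The change should be made before data accrue, because it is cheap and the loss cannot be repaired later.

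**What to change.** 1. Check Figure 2 and the full protocol. If all three arms are already asked about events in the same way at the same times, say so in the safety section.
2. Otherwise, put one identical adverse-event checklist to all three arms at the shared time points already planned: end of treatment, 1 month and 6 months. Keep the wording the same whether follow-up is in person or by telephone.
3. Protect blinding. Answers about soreness after a session or an upset stomach could reveal the arm. Ask the checklist after the blinded outcome ratings are complete, or have it asked by the independent data recorder described under Data collection and management.
4. Base any comparison with the Western medicine arm on these commonly elicited events.
5. Continue to record and report every event noted at a session or volunteered, listed by arm. Compare session-noted events only for test versus sham, where contact is equal.

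**Cost.** One short form at assessments already planned, with no added visits. Recall at the shared time points will miss some mild, transient events, equally in all arms, and drug-arm events during treatment will not be detected any earlier. If earlier detection is wanted, contact must be added on the same schedule in all three arms; one weekly call, for instance, would be 4 × 90 = 360 calls. The fix above does not depend on that.

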#### Data collection and management

The data of the included participants in this study will all be recorded on CRFs, and the clinical trial data will be recorded by an independent third person on a uniformly printed CRF sheet. Excel software will be used to create a database, with data entered independently by two people. All physical CRF texts will be kept in a locked cabinet in the researcher’s office. The Excel database and CRF texts will be authorized only to the data manager and statistician to ensure data security and protection of participant privacy.

#### Statistical methods

According to the prestudy observations, the best effective rate of the test group was 85%, the effective rate of the pseudomanipulative therapy control group was 40%, and the effective rate of the Western medicine group was 47%. The sample size estimation formula for the comparison of multiple sample rates was used to calculate P_max_ = 0.85, P_min_ = 0.40, *α* = 0.05, *β* = 0.10, and *ν* = 3–1 = 2, and the checking of the attached table yielded *λ* = 12.65. The number of sample cases was distributed between the groups according to a ratio of 1:1:1, and a unilateral test was used. *N* = 27 and considering a 10% shedding rate, 30 samples were needed in each group, for a total of 90 in the three groups.

$$n=\frac{2\lambda }{{\left(2\sin^{-1}\sqrt{P_{\max}}-2\sin^{-1}\sqrt{P_{\min}}\right)}^{2}}$$

$$=\frac{2\times 12.65}{{\left(\sin^{-1}\sqrt{0.85}-\sin^{-1}\sqrt{0.40}\right)}^{2}}$$

=26.6,take27

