### Outcome measures

#### Primary outcome

HRV-Related Parameters: This study will utilise a 24-h ambulatory electrocardiograph to measure three distinct groups of HRV parameters, both prior to and following treatment. The primary parameters will be evaluated encompassed the standard deviation of the mean of the R-R intervals per 5-min segment (SDANN), the standard deviation of the R-R intervals (SDNN), the proportion of neighboring R-R interval differences greater than 50 milliseconds as a percentage of the total number of heartbeats (PNN50), and the root mean square of the neighboring R-R interval differences (rMMSD).

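### The sample size and its beta of 0.10 rest on an effective rate that is not a listed outcome, so the stated 90% power does not apply to the HRV primary outcome, which has no stated power

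*Protocol article*

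**What the plan says.** **Sample size (protocol article, Statistical methods).** The inputs are response proportions from pre-study observations: "the best effective rate of the test group was 85%, the effective rate of the pseudomanipulative therapy control group was 40" (40%), and "the effective rate of the Western medicine group was 47" (47%). The method is a formula for proportions: "The sample size estimation formula for the comparison of multiple sample rates was used to calculate". The settings are alpha 0.05, beta 0.10 and nu = "3–1 = 2, and the checking of the attached table yielded" lambda = 12.65, "and a unilateral test was used". The result is 26.6, taken as 27 per group, raised to 30 for 10% dropout, 90 in all.

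**Outcomes.** The abstract (Methods/design) states: "The primary outcome indicators assessed is the HRV-related parameters". The Primary outcome section says: "This study will utilise a 24-h ambulatory electrocardiograph to measure three distinct groups of HRV parameters, both prior to and following treatment". It then names SDANN, SDNN, PNN50 and rMSSD, with none singled out. The secondary outcomes are the NDI, NPQ and HAMA scores. Neither list contains an effective rate or a responder threshold.

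**Analysis (Statistical analysis).** Measurements are compared between groups by one-way ANOVA, or by a rank sum test if not normal, and within groups by paired t test, at p < 0.05. A chi-square test is planned for count data in general, without naming a variable.

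**The concern.** A sample size carries its power only for the endpoint and test it was computed for. Here the calculation is for a binary response, while the primary outcome is continuous and is compared by ANOVA. The article gives nothing that links the two, such as a cut-off on HRV that would define a responder.

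The Conclusion says the results will be used to determine efficacy and to examine whether HRV can serve as a method for assessing the disease. If HRV shows no group difference, the reader must know what size of difference the trial could have found. The only power figure in the article cannot answer that.

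The same paragraph also labels the test one-sided, which does not fit a three-group comparison with 2 degrees of freedom. The Statistical analysis section gives no sidedness for its p < 0.05, so this label is the article's only statement on the matter.

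**Working it through.** **Step 1: reproduce the plan's figure.** Inputs from Statistical methods: P_max = 0.85, P_min = 0.40, lambda = 12.65.

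- n = 2 × lambda / (2 asin√P_max − 2 asin√P_min)²
- Arcsine difference = 2.3462 − 1.3694 = 0.9768; squared, 0.9541
- n = 25.30 / 0.9541 = 26.5, rounded up to 27 (the article prints 26.6, also taken as 27)
- Dropout: 27 / 0.9 = 30 per group, 90 in total

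The arithmetic holds for the effective rate. At 27 per group its power is 90.5% by the arcsine formula. The 47% does not enter that formula. Adding it in a three-group chi-square gives a mean rate of 0.5733, a noncentrality of 27 × 0.11727 / 0.24462 = 12.94, and power of 90.7%.

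**Step 2: check lambda and the sidedness.** The noncentral chi-square with 2 df reaches 90% power at alpha 0.05 when lambda = 12.654, which matches 12.65. That test has no direction, so the one-sided label is wrong. The figure of 27 does not depend on it.

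**Step 3: check the second displayed formula line.** It omits the factor 2 before each arcsine. Read literally, the difference is 0.4884 and n = 106. The printed 26.6 follows the first line, so this is a typesetting slip.

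**Step 4: find what 27 per arm gives for HRV.** The article supplies no HRV difference or SD, so the standardised differences below are assumptions that show the range. The test is the planned three-group ANOVA on one parameter, with normal data, equal variances, alpha 0.05 and degrees of freedom 2 and 78. Let s be the largest between-arm difference in SD units.

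- Middle arm midway: noncentrality = 27 × s²/2 = 13.5 s²
- Two control arms equal: noncentrality = 27 × 2s²/3 = 18 s²

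| s (assumed) | Noncentrality, midway | Power, midway | Noncentrality, controls equal | Power, controls equal |
|---|---|---|---|---|
| 0.3 | 1.22 | 14.8% | 1.62 | 18.4% |
| 0.5 | 3.38 | 34.5% | 4.50 | 44.5% |
| 0.8 | 8.64 | 73.5% | 11.52 | 85.5% |
| 1.0 | 13.50 | 90.8% | 18.00 | 96.9% |

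90% power is reached at s = 0.99 (midway) or s = 0.85 (controls equal). Both correspond to a noncentrality of about 13.15, that is f = √(13.15/81) = 0.40.

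**The case against.** **The article never claims 90% power for HRV.** It ties beta to the comparison of rates. This stands: there is no such claim to withdraw. What is wrong is that the trial's only power figure concerns something outside its outcome lists.

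**The chi-square test for count data is the kind of test that was sized, and a fuller protocol may define the rate.** This stands in part. A reader might infer that the sized test will not be run, but the text does not show that. It shows only that no outcome is attached to it. Condensation does not remove the problem, because the article gives both a complete calculation and complete outcome lists, and the two do not meet.

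**The HRV effect could be large.** This stands. A reader might infer from the 0.5 SD row that the trial is badly underpowered for HRV. The documents do not support that: they give no HRV difference or SD, and at 1.0 SD the ANOVA has more than 90% power. Lower figures from pairwise t tests, or from splitting alpha over four parameters, would describe analyses the article does not plan.

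**The one-sided label and the missing factor 2 leave n unchanged.** This is true. A reader might take 106 per group as the size actually required, but the printed result contradicts that reading. Nor can the label make the ANOVA one-sided; among the planned tests of means it could affect only the paired t tests.

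**Conclusion.** The concern holds as an endpoint mismatch. The 27 per group is correctly computed for the effective rate, and its 90% power does not carry over to the HRV primary outcome, whose power is unstated and cannot be worked out from the article. With 27 evaluable per arm, one parameter and the planned ANOVA at 0.05, 90% power would need a largest difference of about 0.85 to 0.99 SD, which the article neither states nor justifies. The range rests on the assumed position of the middle arm and on normal data with equal variances. If the rank sum test is used instead, the figures are only a guide. The one-sided label is an error of description, and the formula line is a minor misprint.

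**What to change.** 1. Keep 90 participants, and state that beta = 0.10 refers to the effective rate only.
2. Name one of the four HRV parameters as primary and state the standardised difference that 27 per arm can detect with the planned ANOVA: 90% power for a largest between-arm difference of 0.99 SD with the middle arm midway, or 0.85 SD with equal control arms. Convert it to the parameter's own units only if a sourced SD exists; PNN50 is a percentage. Otherwise, state that HRV is not formally powered.
3. If the effective rate remains the sizing basis, define it and list it as an outcome.
4. Delete the statement that a one-sided test was used, and state two-sided 0.05 for the t tests.
5. Minor: restore the factor 2 in the second displayed formula line.

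The cost is protocol wording, plus the choice of one parameter if HRV is to carry a power statement. No extra participants are needed, and allocation and treatment are unchanged. The sponsor gives up the appearance that the primary outcome has 90% power.
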